## Abstract

**Background:**

Numerous randomized trials involving acupuncture treatment for cervicogenic headache (CEH) have been conducted in recent years, but the evidence for its effectiveness is not clear. Hence, we designed a randomized trial to evaluate the efficacy and advantages of acupuncture for treating CEH.

**Design:**

This is a parallel-design, two-arm, patient-assessor blinded, randomized, sham-controlled clinical trial. A total of 166 patients with CEH aged from 18 to 70 will be recruited and assigned randomly into a *jin* acupuncture group and a pseudo acupuncture group at a 1:1 ratio; they will receive 12 sessions of real acupuncture and sham acupuncture for 4 weeks, respectively, during the study. The primary outcomes are pain degree (PD) and pain rate (PR) calculated by the PainVision analyzer, as well as parameters detected by surface electromyography (SEMG). The secondary outcomes will be measured with the short-form McGill Pain Questionnaire (SF-MPQ), range of motion (ROM) of the neck, the Northwick Park Neck Pain Questionnaire (NPQ), the 36-item short-form Health Survey (SF-36), the Self-Rating Anxiety Scale (SAS), and the Self-Rating Depression Scale (SDS). Clinical assessments will be evaluated at baseline and in the fourth week as well as in the eighth and sixteenth weeks. Adverse events will be noted and recorded for the safety evaluation.

**Discussion:**

This study will provide high-quality evidence of the value of acupuncture based on *jin* theory for treating CEH.

**Trial registration:**

Chinese Clinical Trial Registry, ChiCTR1800015316. Registered on 22 March 2018. Updated version AMCTR-IOR-18000157. Registered on 1 April 2018.

**Electronic supplementary material:**

The online version of this article (10.1186/s13063-019-3478-1) contains supplementary material, which is available to authorized users.

## Background

Cervicogenic headache (CEH) refers to a group of syndromes characterized by unilateral preponderance of headache, restricted movement of the neck, and hypersensitivity of the occipital neck region caused by degeneration of the cervical vertebra and detriment of the cervical soft tissue [1]. An epidemiological investigation showed that approximately 2.5% of individuals suffer from CEH, with an age distribution between 30 and 50 years and a ratio of men to women of 1:4 [2]. The International Headache Society (IHS) considers CEH as a special disorder different from common types of headache [3], with published and revised reports in 2004 and 2013, respectively [4, 5]. Although the pathological mechanism of CEH is still disputed, with causes focused mainly on musculoskeletal disorders in the cervical spine [6] or convergence afferent signal disturbance of the trigeminal nerve and the upper cervical nerves [7], there are various interventions being performed according to the accumulated experience, varying knowledge scopes, and professional trends of doctors, such as drugs (including narcotic drugs) [8], nerve block [9], pulse radiofrequency [10], Western medicine [11], acupuncture [12], Tuina [13], and Chinese medicine [14].

As a vital constituent of traditional Chinese medicine (TCM), acupuncture is well known and used in some countries. It has played a very important role in dealing with diseases associated with cervical spondylosis in China [15]. Some clinical trials demonstrated acupuncture to be superior to conventional methods regarding curative effects and unexpected events in the treatment of CEH [16, 17]. *Jin* theory, as an important branch of meridian theory, was demonstrated to be effective in the treatment of pain [18]. Clinically, according to TCM, *jin* disease basically appears as aches, clonuses, spasms, rigidity, relaxation, and limb weakness, symptoms which are very similar to the manifestation of muscle, tendon, myofascial membrane, ligament, and neuropathic lesions. Therefore, from the perspective of functional anatomy, *jin* refers to a complex system combining local anatomical morphology and significant characteristics mainly involving muscles, tendons, myofascial membranes, ligaments, and nerves, etc. [19]. CEH is a kind of *jin* disease, and its pathogenesis is closely related to the *pain point of jin* formed by pathological changes in muscles (cervical extensor muscles, myofascial fascia, and tendons) and nerves (occipitalis major nerve and occipitalis minor nerve) and abnormality of proprioception [19, 20]. The aponeurosis attaches to the articular surface or vertebrae and becomes a stress concentration point due to the great stress caused by keeping the head and neck in a low flexion position. Long-term stress concentration can lead to the occurrence of energy metabolism crises of the muscle fibers, fibrosis of muscles, and other lesions, which contribute to form the tension zones and sensitive points of muscle fibers (*gather* and *knot* in TCM), inducing pain and distal referred pain when pressed [21]. In addition, when tension and spasm occur in the muscle where the nerve passes through, compression or stimulation symptoms are prone to be produced at the outlet of the nerve [22]. Therefore, taking the outlet of the nerve as an acupoint to perform acupuncture should show positive significance for the relief of symptoms of CEH.

At present, more attention is paid to the evaluation of headache, ignoring symptoms and signs of the neck and occipital region. Also, abundant non-acknowledged therapies have been adopted conventionally in control groups, which has weakened the clinical study quality of acupuncture for CEH. In this study, we focus on the main and secondary symptoms and signs involving headache as well as pain and stiffness of neck-occipital region, and we aim to verify the value of acupuncture based on *jin* theory. The study and its final conclusion will provide a reasonable and high-quality clinical trial contributing to the popularization and application of acupuncture for CEH.

## Methods and design

### Study design

This is a two-arm, parallel-design, patient-assessor blinded, clinical randomized controlled trial (RCT) aiming to evaluate the differences of efficacy between acupuncture based on *jin* theory and sham acupuncture for CEH. A total of 166 patients will be recruited from the Department of Acupuncture-Tuina and Rehabilitation of the first affiliated hospital of Yunnan University of Traditional Chinese Medicine. Recruitment advertisements will be placed on the network and recruitment posters. Eligible participants in each group will have an equal chance of being allocated randomly to obtain real or sham acupuncture treatment. The primary outcomes are objective parameters detected by devices (PainVision analyzer and surface electromyography [SEMG]); the secondary outcomes are assessed by scales. This study will last 16 weeks including 1 week for baseline, 4 weeks for treatment, and 12 weeks for follow-up. Methods and data from this study will contribute to the feasibility and simplicity of acupuncture for CEH patients. This protocol was registered on 22 March 2018 (ChiCTR1800015316, AMCTR-IOR-18000157). The updated protocol was changed on 26 April 2019. Figure 1 shows a flowchart of the study. Additional file 1 provides the Standard Protocol Items: Recommendations for Interventional Trials (SPIRIT) checklist; Additional file 2 shows the Standards for Reporting Interventions in Controlled Trials of Acupuncture (STRICTA) checklist.

**Fig. 1 Fig1:**
[figure not shown]
Flowchart of this trial

### Participants

#### Study population and sample size

Patients with CEH meeting the diagnosis of the International Classification of Headache Disorders, 3rd edition (ICHD-3) formulated by the IHS [5] will be enrolled. The reduction of the visual analog scale (VAS) average score was 6.37 to 2.31 after triple acupuncture treatment compared to 6.37 to 2.52 for conventional acupuncture treatment according to a relevant study [23]. We propose to set the VAS of the short-form McGill Pain Questionnaire (SF-MPQ) average score as 2 and 4 for the *jin* acupuncture group and pseudo acupuncture group, respectively. Given a significance level of 0.05, a standard deviation of 5, and power of test of 0.95, and considering a 10% loss rate, 166 participants in total are needed with 83 in each group.

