### Outcome measures

#### Primary outcome measures

The following primary outcome measures will be used to evaluate the effectiveness at weeks 4, 8, and 16 after randomization, respectively, compared with the baseline.Pain degree (PD) and pain rate (PR): With a measurement accuracy of 0.1 μA, 0.3 ms pulse width, and 50 Hz pulse frequency, both indicators will be calculated using the current perception threshold (CPT) and pain equivalent current (PEC) with the PainVision analyzer according to the following formula [24, 25]:$$ PD=\frac{PEC- CPT}{CPT}\times 100\kern0.5em PR=\frac{PEC}{CPT} $$Surface electromyography (SEMG): With the patient in a prone position, a sticker will be placed on the affected side cervical extensor muscles (2 cm lateral to the posterior midline of the neck). The SEMG signal will be detected through an eight-channel module ME6000 biomonitor (Mega Electronics Ltd., Kuopio, Finland) as the operator successively applies 25% (maximum voluntary contraction, MCV), 50% MCV, and 100% MCV resistance, respectively, to the posterior occipital area. The system will automatically record and transmit the signal to generate the original image, and indicators of muscle fatigue including median frequency (MF), mean power frequency (MPF), average rectified value (ARV), and root mean square (RMS) will be calculated by Mega Win software for statistical analysis [26].

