#### Secondary outcomes

The secondary outcomes are measured as described below.Short-form McGill Pain Questionnaire (SF-MPQ): This questionnaire comprises Pain Rating Index (PRI), Present Pain Intensity (PPI), and VAS items. The PRI includes sensory and affective parts with negative, mild, moderate, and severe pain (from 0 to 3) representing the degree, while the PPI values from 0 to 5 represent different degrees of pain. A VAS number of 0 represents no pain, and 10 represents unbearable pain [27].Northwick Park Neck Pain Questionnaire (NPQ): The NPQ has been commonly used in clinical research and has shown high validity and practicability for neck pain assessment [28]. It consists of nine items involving the degree and duration of pain, numbness of upper extremities, sleep, and social activities as well as other quality of life characteristics. The total score is 100, and high scores mean severe disability from neck pain.Range of Motion (ROM) of the neck: This reliable and valid tool, consisting of two gravity goniometers and a compass goniometer, is used to assess the degree of cervical spine movement involving the cervical movement distance of bilateral rotation and flexion without undergoing pain [29]. This measurement is performed by a specific senior researcher, and the mean values will be recorded to facilitate the analysis.Short-form 36-item Health Survey (SF-36): The health-related quality of life and correlation factors including physical function and daily functioning are evaluated by a 5-point scale [30].Self-Rating Anxiety Scale (SAS) and Self-Rating Depression Scale (SDS): The SAS is a relatively simple clinical tool to analyze the subjective symptoms of patients. It is applicable to adults with anxiety symptoms and has a wide range of applications. The SDS can fairly directly reflect the subjective feelings of patients with depression and their changes in treatment. It is mainly applicable to adults with depressive symptoms. Compared to the SDS, the SAS can better reflect the subjective feelings of patients with anxiety tendencies [31].

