### Statistical analysis

All of the data will be entered in the CRFs and input into the database by two independent researchers, calculated by means of the SPSS 25.0 software package. Data analysis and comparison will be performed based on the intention-to-treat (ITT) population and the per protocol (PP) population, contributing to the integrity and objectivity of this study. The ITT population consists of all participants who have been randomized and received at least one session of acupuncture after the baseline. PP refers to the patients who have completed the study and did not violate the protocol. A two-sided value of *P* < 0.05 will be defined as the statistical significance, categorical variables in two groups will be analyzed by chi-squared or Fisher’s exact test, normally distributed data will be analyzed by Student’s *t* test, and non-normally distributed data by the Mann-Whitney *U* test. Continuous variables in two groups including primary outcomes (the PainVision and SEMG parameters) and secondary outcomes will be compared using a general linear model with repeated measurement methods at all time points.

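### The only sample-size calculation concerns a secondary outcome (SF-MPQ VAS), so the stated 95% power does not apply to the PainVision and SEMG primary outcomes; nor do its own inputs give 95% for the VAS.

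*Protocol article*

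**What the plan says.** The protocol article's section on study population and sample size contains the only calculation. It cites VAS results from an earlier acupuncture study and then says: "We propose to set the VAS of the short-form McGill Pain Questionnaire (SF-MPQ) average score as 2 and 4" for the jin and pseudo acupuncture groups respectively. With significance level 0.05, SD 5, power 0.95 and 10% loss, it arrives at 166 patients, 83 per group.

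The VAS belongs to the SF-MPQ. Under the heading Secondary outcomes the article explains: "This questionnaire comprises Pain Rating Index (PRI), Present Pain Intensity (PPI), and VAS items". The VAS runs from 0 to 10.

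The ranking of outcomes is the same wherever it appears:

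- Abstract, Design: "The primary outcomes are pain degree (PD) and pain rate (PR) calculated by the PainVision analyzer", together with SEMG parameters. The SF-MPQ is listed among the secondary outcomes.
- Study design: "The primary outcomes are objective parameters detected by devices (PainVision analyzer and surface electromyography [SEMG]); the secondary outcomes are assessed by scales".
- Statistical analysis: "including primary outcomes (the PainVision and SEMG parameters) and secondary outcomes" are to be compared with a repeated-measures general linear model.

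**The concern.** A power statement belongs to one variable, with its own target difference and its own SD. Here it belongs to a 0-10 self-rating, while the trial is to be judged on ratios of electrical currents (PD and PR) and on muscle-fatigue indices from SEMG. The article offers no correlation or argument linking the VAS to these measures, so neither the size of effect nor the variability can be carried across.

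The consequence lies in interpretation. If PD or an SEMG index shows no difference, a reader who takes 95% as the trial's power will treat that as strong evidence of no effect of the assumed size. Nothing in the article supports that reading. The Discussion's promise of strong evidence has no stated precision behind it for the primary question.

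**Working it through.** **1. Reproducing the stated figure for the VAS.**

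Inputs from the sample-size section: difference 4 - 2 = 2, SD 5, alpha 0.05, power 0.95, loss 10%. Two-sided testing comes from the Statistical analysis section, and 1:1 allocation from the randomization section.

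n per arm = 2 × (z for alpha + z for power)² × SD² / difference² = 2 × (1.960 + 1.645)² × 25 / 4 = 162.4, so 163 (164 with the t distribution).

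Allowing for 10% loss: 163 / 0.9 = 181.1, so 182 per arm or 364 in total. The article states 83 per arm.

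Other conventions do not reach 83 either:

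| Test | Power | n per arm | n per arm after 10% loss |
|---|---|---|---|
| Two-sided | 0.95 | 163 | 182 |
| Two-sided | 0.90 | 132 | 147 |
| Two-sided | 0.80 | 99 | 110 |
| One-sided | 0.95 | 136 | 152 |
| One-sided | 0.80 | 78 | 87 |

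**2. Power that the planned n gives for the VAS on the stated inputs.**

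Standardised difference = 2 / 5 = 0.4. Evaluable per arm after loss = 83 × 0.9 = 74.7, taken as 75.

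Power ≈ Φ(0.4 × √(n/2) - 1.960):

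- n = 83: 0.4 × √41.5 = 2.577; Φ(0.617) = 0.73 (t test 0.73).
- n = 75: 0.4 × √37.5 = 2.449; Φ(0.489) = 0.69 (t test 0.68).

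**3. What the planned n gives for a device outcome.**

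Power cannot be computed in PD, PR or SEMG units, because no difference or SD is given. It can be stated in SD units. With 75 per arm, two-sided 0.05 and one comparison at one time point, detectable difference = (1.960 + z for power) × √(2/75), where √(2/75) = 0.163:

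- 80% power: (1.960 + 0.842) × 0.163 = 0.46 SD (t test 0.460).
- 95% power: (1.960 + 1.645) × 0.163 = 0.59 SD (t test 0.593).

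The power curve at the same n, for assumed standardised differences (illustration only; the article supports none of these values):

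| Difference (SD) | 0.2 | 0.3 | 0.4 | 0.5 | 0.6 |
|---|---|---|---|---|---|
| Power (normal approximation) | 23% | 45% | 69% | 86% | 96% |

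**4. PD and PR.**

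From the article's formulas, PD = 100 × (PEC - CPT) / CPT = 100 × (PR - 1). PR is PD rescaled, so a power statement in SD units for PD holds for PR without change. It does not carry over to the SEMG indices.

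**The case against.** **The device outcomes are not shown to be underpowered.** This stands. Unknown power is not low power, and a reader might infer from the 23% at 0.2 SD that the trial is too small. That effect size is an arbitrary illustration. The planned model also uses repeated measurements, so a single-time-point calculation is only an approximation to the power of the actual analysis.

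**The VAS looks like the one properly powered endpoint, so it should be made primary.** A reader might infer this, but the documents do not support it. The VAS is the only endpoint with a power calculation, and that calculation does not reproduce. Its SD of 5 is also impossible on a 0-10 scale with these means: the largest attainable SDs are √(2 × 8) = 4.0 and √(4 × 6) = 4.9. For the same reason it would be wrong to conclude that the VAS truly has 68% power. An SD of about 3.4 would give 95% with 75 per arm, but the article does not state that SD. The Study design section deliberately chooses device measures as primary, and the Trial status section says recruitment began in April 2018 and is ongoing. Changing the primary outcome now would be an outcome switch, not a correction.

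**The article openly names the VAS and claims nothing about PD or SEMG.** This is true of the wording. But the VAS calculation is the only justification given for n, and a reader will take its power as the trial's power.

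**The full protocol may hold more.** It may, but the point rests on what the article states. It presents a complete calculation, and that calculation is for a secondary outcome.

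**Conclusion.** The point holds. The only power the article states does not attach to the outcomes that decide the trial, and no target difference, SD or power is given for any of those. The stated 95% also fails on its own terms: the article's inputs give about 73% with 83 per arm and 68% with 75, against the 163 to 164 evaluable per arm that 95% would need.

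For a primary variable, the most that can be said is that the fixed n gives 80% power at 0.46 SD and 95% at 0.59 SD. This assumes 75 evaluable per arm, two-sided 0.05 spent on a single comparison, and one time point. If alpha were split equally over six parameters (PD, PR, MF, MPF, ARV, RMS), the 95% figure would be about 0.70 SD. Whether any of these differences is realistic or clinically relevant for PD cannot be judged from the article.

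**What to change.** Keep the device outcomes as primary and n at 166. In the sample-size section:

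1. Designate PD as the variable to which the power statement applies.
2. Replace the 95% claim with what the fixed n delivers for PD: about 75 evaluable per arm, two-sided 0.05, single-time-point comparison, 80% power at 0.46 SD and 95% at 0.59 SD.
3. If figures in PD units are wanted, convert these with a blinded pooled SD from patients already measured. The section on data collecting and monitoring bars researchers, including statisticians, from seeing the data during evaluation, so the SD must be extracted by someone permitted to see the data.
4. State that the VAS calculation concerns a secondary outcome, and do not attach 95% power to it on the present inputs.

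The cost is a dated amendment to the wording. No patients, procedures or visits are added, since outcomes are already assessed at baseline and weeks 4, 8 and 16. The downside is that the stated power becomes less favourable than the 95% now published.

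### The planning SD of 5 is impossible on a 0–10 VAS with means of 2 and 4, so the stated 95% power at 166 patients does not rest on an attainable SD; the sham mean of 4 is an unsupported assumption

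*Protocol article*

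**What the plan says.** The section on study population and sample size in the protocol article first reports an earlier trial in which the mean VAS fell from "6.37 to 2.31 after triple acupuncture treatment compared to 6.37 to 2.52 for conventional acupuncture treatment". It then proposes, for the VAS item of the SF-MPQ, an "average score as 2 and 4 for the *jin* acupuncture group and pseudo acupuncture group, respectively". The remaining inputs are alpha 0.05, "a standard deviation of 5, and power of test of 0.95", with a 10% loss rate. The result is 166 patients, 83 per group.

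The scale is defined under secondary outcomes: "A VAS number of 0 represents no pain, and 10 represents unbearable pain". The sample-size section does not say whether the test is one- or two-sided, but the statistical analysis section does: "A two-sided value of *P* < 0.05 will be defined as the statistical significance". No source is given for the SD of 5 or for the sham mean of 4.

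**The concern.** A bounded scale limits how far scores can spread around a given mean. An SD of 5 on a scale only 10 points wide is the absolute maximum. It needs a mean of exactly 5, with half the patients at 0 and half at 10. The plan pairs it with means of 2 and 4, where that spread cannot arise.

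The SD largely determines the sample size. If it is impossible, the stated power describes no trial that could take place. Correcting only the sample-size arithmetic while keeping SD 5 would carry the same defect into a new and much larger number. The lead-in to the calculation also invites a reader to think that the 2-point difference comes from the earlier trial, whose two arms finished far closer together than that and had no sham control.

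**Working it through.** **Inputs.** Difference 4 − 2 = 2, SD 5, alpha 0.05, power 0.95 and loss 10% (sample-size section); two-sided testing (statistical analysis section); VAS range 0 to 10 (secondary outcomes); 1:1 allocation (randomization section). Evaluable patients per arm: 83 × 0.9 = 74.7, taken as 75.

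**Step 1: reproduce the plan's figure.** Normal approximation, per arm:

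n = 2 × SD² × (1.960 + 1.645)² / difference² = 2 × 25 × 12.99 / 4 ≈ 162.4, so 163 per arm (164 with the t distribution).

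With 10% loss: 163 / 0.9 = 181.1, so 182 per arm and 364 in total. The stated 166 is not reproduced. A one-sided test gives 136 per arm, or 304 in total with loss, which does not match either. With SD 5 and a difference of 2, two-sided t-test power is about 68% at 75 per arm (69% by the normal approximation) and about 73% with all 83.

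**Step 2: the largest SD the scale allows.** For scores between 0 and 10 with mean m, the maximum SD is √(m(10 − m)), reached only if every patient scores exactly 0 or 10.

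- Mean 2: √(2 × 8) = 4.00
- Mean 4: √(4 × 6) = 4.90
- Pooled over equal arms: √((16 + 24)/2) = 4.47

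Using the n − 1 divisor at 75 patients raises the first two only to 4.03 and 4.93. SD 5 exceeds every one of these limits.

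**Step 3: what the cited study supplies.** As quoted, both arms start at 6.37 and end at 2.31 and 2.52. The end values differ by 2.52 − 2.31 = 0.21. Both arms are active acupuncture. No sham mean and no SD are quoted. The planned *jin* mean of 2 lies near 2.31; nothing quoted bears on the sham mean of 4.

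**Step 4: power at the planned size with other SDs.** Two-sample t-test, two-sided 0.05, difference 2. The SDs below are assumptions, because the article gives no attainable value.

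| SD | Power at 75 per arm | Evaluable n per arm for 95% power |
|---|---|---|
| 4.47 (mathematical limit) | 78% | 131 |
| 4.0 | 86% | 105 |
| 3.5 | 93.5% | 81 |
| 3.0 | 98% | 60 |
| 2.5 | above 99% | 42 |

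Power of 95% at 75 per arm requires an SD of about 3.4 or less.

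**The case against.** **The figures might be change scores.** A change on this scale can range from −10 to 10, so an SD of 5 would then be possible. The text does not support this reading. It sets average scores, follows them from end values of 2.31 and 2.52, and gives the lower figure to the *jin* arm. Read as reductions, 2 against 4 would make sham the better treatment.

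**The 2-point difference is openly the sponsor's proposal.** This stands. The article reports the earlier trial and then proposes its own means; a target difference may be chosen without a source. A reader might infer that the sponsor misreported the cited study or claimed to take the difference from it. The wording does not go that far. The fair criticism is that no reason is given for the sham mean.

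**Too large an SD is conservative.** This also stands. A larger SD inflates the required number, so a reader who infers from the impossible SD alone that the trial is underpowered goes beyond the documents. The 78% row in the table is a mathematical limit with every score at 0 or 10, not a planning scenario.

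**Most inputs are ordinary.** Alpha, target power, loss rate and allocation are all unremarkable. It would be too strong to say that the calculation has no valid input: one input is impossible and one is unsupported.

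**Conclusion.** The point holds in this form. SD 5 is impossible for the stated means and scale; this follows from the article's own figures and needs no outside assumption beyond reading 2 and 4 as scores on the 0–10 VAS. The sham mean of 4, and so the 2-point difference, is an assumption for which the quoted study offers no support. The claimed 95% power at 166 therefore rests on no attainable SD, and it is not obtained from SD 5 either (about 68% at 75 evaluable per arm; about 364 patients in total would be needed).

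Whether 166 is adequate for this VAS comparison is open. If the true difference is 2, it is enough for 95% power at an SD up to about 3.4 and falls short above that. The article does not say where the SD lies. The documents show neither that the trial is too small nor that it is larger than needed. All of this concerns the VAS, which is a secondary outcome; the calculation makes no statement about the PainVision or SEMG primary outcomes.

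**What to change.** Replace SD 5 with an attainable value, state its source, and restate the power at N = 166 for a difference of 2 across a range of SDs labelled as assumed, as in the table above. Name the time point to which the means of 2 and 4 refer. Say plainly that the sham mean of 4 and the 2-point difference are assumptions, and separate them from the cited study. State that 166 does not give 95% power at SD 5.

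A blinded SD from patients already assessed is one possible source, since recruitment opened in April 2018. Two cautions apply. An SD taken over both arms together includes the difference between them: with equal arms and a gap of 2 the variance rises by 2²/4 = 1, so a within-arm SD of 2.5 would appear as √(6.25 + 1) ≈ 2.7. And the section on data collecting and monitoring bars researchers, statisticians among them, from the data during evaluation, so access would have to be arranged consistently with that rule.

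The cost is revised wording, a short calculation and, if the blinded route is taken, an access arrangement. No unblinding and no extra patients are needed. The downside is that the restated power may be less favourable than 95%.

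### The stated inputs do not give 83 per group at 95% power: they need about 182 to 183 per group, and the SD of 5 does not fit the 0–10 scale

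*Protocol article*

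**What the plan says.** The protocol article gives its whole sample-size justification under Study population and sample size. It works on the VAS item of the SF-MPQ and sets the "average score as 2 and 4 for the *jin* acupuncture group and pseudo acupuncture group, respectively". It continues: "Given a significance level of 0.05, a standard deviation of 5", then "power of test of 0.95, and considering a 10% loss rate, 166 participants in total are needed with 83 in each group". That section does not state sidedness. The Statistical analysis section does: "A two-sided value of *P* < 0.05 will be defined as the statistical significance". Allocation is 1:1 between two parallel arms.

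Two other sections bear on the point. Secondary outcomes defines the VAS as running from 0 (no pain) to 10. Primary outcome measures lists the PainVision indices and the SEMG parameters, so the variable used for the sample size is a secondary outcome.

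**The concern.** The section gives every input that a two-group calculation needs, so its result can be checked directly. A difference of 2 with an SD of 5 is a standardised effect of 0.4, and 83 per group looks far too few for 95% power at that effect.

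This is the only power statement in the article and the only support for enrolling 166 patients. A reader who accepts it will take the chance of missing a 2-point VAS difference to be 5%. If the inputs do not support that, the stated property is wrong, and a null VAS result would be given more weight than the stated design supports.

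**Working it through.** **Inputs.** From Study population and sample size: means 2 and 4, so Δ = 2; SD σ = 5; α = 0.05; power 0.95; loss 10%; 83 per group. From Statistical analysis: two-sided testing. From the randomisation section: 1:1 allocation. The section names no formula, correlation or baseline adjustment.

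**Attempt to reproduce 83 per group.** For two independent means,

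n per group = 2(z₀.₉₇₅ + z₀.₉₅)² σ²/Δ² = 2 × (1.960 + 1.645)² × 25/4 = 162.4, so 163.

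The exact calculation with the noncentral t distribution gives 164. Allowing for loss, 163/0.9 = 181.1, so 182 per group (364 in total), and 164/0.9 = 182.2, so 183 per group (366 in total). The stated 166 is about 45% of that (166/366 = 0.454).

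**Other conventions for the same Δ and σ** (normal approximation):

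| Test and power | Evaluable per group | Randomised per group | Total |
|---|---|---|---|
| Two-sided, 95% | 163 | 182 | 364 |
| One-sided, 95% | 136 | 152 | 304 |
| Two-sided, 90% | 132 | 147 | 294 |
| Two-sided, 80% | 99 | 110 | 220 |
| One-sided, 80% | 78 | 87 | 174 |

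Inflating by N × 1.1 instead of N/0.9 changes these by only one or two per group. None gives 83. The nearest needs both a one-sided test and 80% power, and the article states neither.

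**Power at the stated size.** 83 × 0.9 = 74.7, so 74 or 75 evaluable per group. With 75, the standard error is 5 × √(2/75) = 0.816 and Δ/SE = 2.449. The normal approximation gives Φ(2.449 − 1.960) = Φ(0.490) = 0.688. The t test gives 0.682 with 75 per group, 0.676 with 74, and 0.726 with all 83.

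**Is an SD of 5 possible?** A variable confined to 0–10 with mean m has an SD of at most √(m(10 − m)):

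- mean 2: √(2 × 8) = 4.0
- mean 4: √(4 × 6) = 4.9
- both arms at their maximum: pooled SD √((16 + 24)/2) = √20 = 4.47

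So 5 cannot be the SD of raw scores in either arm (apart from a negligible small-sample correction).

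**Power across SDs that could occur** (two-sided t test, Δ = 2):

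| SD | 75 per group | 83 per group |
|---|---|---|
| 5 (as stated) | 68% | 73% |
| 4.47 (largest possible) | 78% | 82% |
| 4 | 86% | 89% |
| 3.5 | 94% | 96% |
| 3 | 98% | 99% |

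With 75 per group, 95% power is reached at an SD of about 3.4 (3.38 by the t test).

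**The case against.** **The real power may be much better than 68%.** This stands. Since SD 5 cannot occur for raw scores on this scale with these means, 68% describes the stated inputs and not the trial. A reader might infer that the trial will miss a true 2-point VAS difference about one time in three. The documents do not support that, because it holds only at an SD that the scale rules out. But the objection does not rescue the section: it shows that a second figure in the calculation needs correcting. At the largest possible SD, power is still well short of 95%.

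**The planned analysis is a repeated-measures model, not a t test at one visit.** This is also true, so 68% is not the power of the planned analysis. Adjusting for baseline or averaging over visits could bring the requirement near 83. For example, three post-baseline visits with baseline adjustment and an assumed common correlation of 0.3 would need about 80 per group including loss. The article gives no correlation, and its calculation claims no such gain, so none can be credited to it.

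**An article condenses the full protocol.** Here nothing is omitted. A complete set of inputs is printed with a result that does not follow from them.

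**How 83 arose.** A reader might suppose that a one-sample formula was used, or that a per-group 163 was taken as a total. The article names no formula, and the exact one-sample requirement (83.2) rounds up to 84, not 83. Neither explanation can be verified and the point does not need one.

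**Conclusion.** The point holds in this form: the printed inputs and the printed sample size disagree. For 95% power the inputs require 163 to 164 evaluable, or 182 to 183 randomised, per group. At 83 per group they give about 68% power after 10% loss and 73% without loss. This rests on a two-sided comparison of two independent groups at one time point, with the means, SD and loss as stated.

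The actual power for the VAS is not known from the document, because the SD must be below 5. With 75 evaluable per group it is about 78% at the maximum pooled SD, 86% at SD 4, and 95% only at about 3.4 or less.

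A reader might also infer that the trial is underpowered for its primary outcomes. That does not follow: the calculation concerns the VAS, and neither 95% nor 68% says anything about the PainVision or SEMG comparisons. The correction is needed because a stated design property is wrong on the article's own figures.

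**What to change.** Keep 166 participants and correct the justification in Study population and sample size:

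- Delete the claim that 166 gives 0.95 power at an SD of 5.
- State the SD actually intended, give its basis, and reconcile it with the 0–10 scale and means of 2 and 4.
- Report the power that matches that SD with about 75 evaluable per group, stating that the test is two-sided. If SD 5 is kept, the figure is 68% (73% with no loss) and the text must say what that SD refers to, since it cannot be that of raw scores. A claim of 95% requires an SD of about 3.4 or less.
- Say that the figure applies to the SF-MPQ VAS, a secondary outcome.
- If a gain from repeated measures or baseline adjustment was intended, state the correlation and the formula.

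The cost is wording only, with no extra patients and no change to conduct. The stated power becomes less favourable unless a smaller SD can be justified.
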